### Exclusion criteria

Participants with any of the following conditions will be excluded:Balance dysfunction caused by other encephalopathy, such as brain tumor, brain trauma, brain parasitic diseases;Vestibular problems;Existed disease which may affect training, such as serious joint disease of the lower limbs, arthritis or joint damage, the canal stenosis of lumbosacral vertebral and so on;Serious vision or hearing impairment that would impede full participation;Receptive aphasia (inability to understand instructions);Participated in Tai Chi training in latest 6 months;Severe complications after stroke, such as severe pulmonary infection, shoulder hand syndrome, and lower limb venous thrombosis;Severe medical condition (e.g. Serious heart disease; heart, liver or kidney failure; malignant tumor; gastrointestinal bleeding);Participated in other clinical researches that would affect this trail; Mini-Mental State Exam score ≤ 24.

### Randomization and allocation concealment

Participating CHCs are randomly assigned to either the intervention or the control arm by a 1:1 ratio. Random allocation sequence will be produced by an independent statistician via the PLAN sentences of the statistical software SAS 8.2, who works in the Evidence-Based Center of FJTCM. The randomization program of CHCs will be managed by a specified project manager who is not involved in the recruitment program of this trail, and be concealed to the screeners and outcome assessors. Randomization into the Tai Chi Yunshou exercises training is based on the CHC in which the patient lives. Study objectives, intervention, and data assessment pertain to the individual patient level.

### Blinding

Although it is impossible to blind the participants and exercise coaches in this trial, the exercise coaches will be not involved in the assessment of outcome. At the same time, the outcome assessors and the statistic analyzers will be not involved in the participants’ screening and allocating. The random allocation sequence will be safekeeping by a specified project manager, who is irrelevant with the recruitment, intervention, assessment and statistic analysis. Furthermore, the intervention group will be replaced by the alphabet A or B as blind code of allocation. The blind code will be disclosed when the statistic analysis is completed.

### Intervention

Participants will be allowed to continue routine medications and maintain usual visits with their primary care physicians throughout the study. The Tai Chi Yunshou exercises will be applied to the participants in the intervention group. While participants allocated in the control group will receive balance rehabilitation training. Health education will be provided to all individuals throughout the intervention period.

### Health education

Information will be disseminated to the individuals in all participating CHCs by putting up posters in communities’ public places where people often congregated and distributing pamphlets to each participant. Neurologists or therapist will hold 2 lectures monthly in the community to spread knowledge on the concept, epidemiology, etiology, common symptoms, diagnosis, treatments and precautions of stroke. We encourage individuals to conduct self- management, instructing their families and themselves how to get along with long-term health problems actively.

### Intervention group

The participants in the intervention group will accept a 12-week Tai Chi Yunshou exercises training with a frequency of 5 days per week and 60 minutes one day. The training scheme originated from the 24 forms simplified Tai Chi exercise, which is recommended as the popularity health sport by General Administration of Sport of China (Figure 2) [28,29]. Five qualified coaches who have engaged in the physical education over 5 years will teach the participants of correct Tai Chi Yunshou postures in CHCs during the whole intervention period. Each session included a 15 min warm-up time, then training 45 min continuously. The coach could adjust the length of the training time based on patients’ personal situation, and allocate properly. Individuals who have difficulty in completing the exercise continuously will be allowed to finish intermittently. But each session must last at least 15 min. All patients have 5 min to rest after training. One supervisors will be in charge of the management of training spot to guarantee the quality of Tai Chi Yunshou exercise training.

**Figure 2 Fig2:**
[figure not shown]
**Tai Chi Yunshou exercise.**

### Control group

The balance rehabilitation training will be applied to the participants in the control group, in which the training will be performed in the CHCs. Therapists are responsible for the implementation of a 60-minute practice session five times a week for 12 weeks. The training scheme originated from ‘Technical specification of Common rehabilitation therapy’ (2012) published by Chinese Association of Rehabilitation Medicine [30]. The treatment plan consists of static and dynamic balance function training. Each training session includes 5–15 minutes of warm-up time and 5–15 minutes of rest time, adjusted according to the patient’s fatigue level.

### Follow-up

All participants will enter 12-week unsupervised follow-up period right after the end of intervention. Telephone follow-up will be performed once a week and home visits once a month. Throughout the follow-up period, patient’s current physical and mental status, rehabilitation exercises usage, the quality of life, compliance behavior and usage of drug will be recorded.

### Outcome assessment

The variables in this trial consist of basic characteristic, primary outcome and secondary outcomes. The basic characteristic will be obtained at baseline (before intervention) via a questionnaire (Table 1). The primary and secondary outcomes consist of balance function, motor function, cardiopulmonary function, quality of life, and so on. All outcomes will be measured at baseline and 4-weeks, 8-weeks, 12-weeks, 6-week follow-up, and 12-week follow-up, respectively. Balance and proprioception tests, Cardiopulmonary function, three-dimensional gait analysis will be assessed by experienced operators at the Evaluation Department of Rehabilitation Hospital Affiliated to FJTCM. Other outcomes will be assessed by therapist in The Rehabilitation Hospital Affiliated to FJTCM, The First Affiliated Hospital of Henan University of TCM, and The Second Affiliated Hospital of Shandong University of Traditional Chinese Medicine. All outcome assessors or operators are blinded to the allocation results of participants. A summary of all measurements in this trial is shown in Tables 2 and 3.

**Table 1 Tab1:** **Baseline descriptive data**

**Data**	**Content**
General data	CHC in which patients are recruited from, the date screening, patient’s address, name of accompanying, family members or the patient’s telephone number
Demographic data of subject	Gender, age, height ,weight, nationality, level of education and profession
Assessment of balance function before test	The ability to stand independently or with auxiliary, how many metres could walk with or without aids
Other	Previous treatment and duration of stroke, injury site of cerebrum, type of stroke and number of stroke

**Table 2 Tab2:** **The first part of study flow**

**Items**		**Before enrollment(weeks)**	**Intervention period (weeks)**	**Outcome assessment(weeks)**	**Intervention period (weeks)**	**Outcome assessment (weeks)**
		**−2-(−1)**	**1-4**	**4**	**5-8**	**8**
Recruitment		×				
Inclusion criteria		×				
Exclusion criteria		×				
Informed consent		×				
Basic characteristic variables		×				
Randomization and allocation concealment		×				
Primary outcomes	Berg balance scale	×		×		×
Secondary outcomes	Simplified Fugl - Meyer motor function assessment	×		×		×
	Modified barthel index	×		×		×
	The Medical outcomes study 36-Item Short-Form health survey	×		×		×
	Beck depression inventory	×		×		×
	Modified falls efficacy scale	×		×		×
	Single leg stance test	×		×		×
	Timed-Up-and-Go Test	×		×		×
	Blood glucose and blood lipid	×		×		×
	Proprioception function	×				
	Cardiopulmonary function	×				
	Gait analysis	×				
Adverse events recorded			×		×	
Medication and fall self-report			×		×	
Rehabilitation costs questionnaire			×		×

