### Economic evaluation

The direct costs and indirect costs of the interventions will be investigated throughout the trial. Direct costs include the length of any hospital stay, emergency department visits, general medical treatment, visits to a specialized physician, nursing care and so on. And the number of workdays lost by participants and their families during rehabilitation will be used to assess indirect costs. All participants will be required to record their drug use, frequency of falling per week or any consumption of medical resources during the intervention period.

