### Statistical analysis

The data will be analyzed at the patient level by a statistician working in the Center of Evidence-based Medicine of FJTCM, who is not involved in this trial. The primary analysis will compare the proportion of patients improved of balance function at the 12-week after treatment using a mixed-effects logistic regression model in the intention-to-treat sample (including all randomized patients). Treatment condition (intervention versus control) will be treated as a fixed effect. Baseline severity of balance dysfunction will be included as a covariate and variation among patient clusters (recruited by the same CHCs) will be modeled through random effects. Potential confounding for other measured cluster-level variables such as population size will be adjusted. Continuous outcomes will be analyzed according to the same scheme, but in linear rather than logistic regression models. Item-level missing data in psychometrically sound instruments will be treated in compliance with the corresponding manuals. If no recommendations are available, the expectation-maximization (EM) algorithm will be used to impute up to 30% of missing item responses. Unit-level missing data (patients not providing data for a whole measurement point due to dropping out of the study, for example) will be imputed via the EM algorithm using existing information from the baseline assessments. Further secondary analyses will include analyses in the per-protocol (completer) sample to test the robustness of the primary findings. No interim analysis is planned. Intervention-related data are stored and analyzed separately. All analyses will be implemented using SAS software (version 8.2, SAS Institute, Cary, NC, USA).

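### Costs, falls and drug use are first recorded in weeks 1–4, so a cost or fall comparison between 5 and 5 health centers cannot be adjusted for its own pre-trial level (low priority)

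*Protocol article*

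**What the plan says.** The Outcome assessment section presents Tables 2 and 3 as the summary of everything measured. In Table 2 every primary and secondary outcome has a mark at weeks −2 to −1. The rows "Medication and fall self-report" and "Rehabilitation costs questionnaire" do not. They are marked for weeks 1–4 and 5–8 in Table 2, and for weeks 9–12, 13–18 and 19–24 in Table 3.

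The Economic evaluation section fits this schedule. It states that "The direct costs and indirect costs of the interventions will be investigated throughout the trial", and that participants will "record their drug use, frequency of falling per week or any consumption of medical resources during the intervention period".

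Table 1 lists the baseline questionnaire. Its clinical history line reads "Previous treatment and duration of stroke, injury site of cerebrum, type of stroke and number of stroke". No item covers earlier falls, earlier use of health care or earlier cost.

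The Statistical analysis section adjusts for baseline severity of balance dysfunction, models CHCs as random effects, and adjusts for measured cluster-level variables. Data missing for a whole measurement point "will be imputed via the EM algorithm using existing information from the baseline assessments".

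**The concern.** A patient's earlier spending and earlier falls are natural predictors of later spending and falls. The schedule starts both records only once training has begun, so neither can serve as its own baseline covariate.

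This weighs more here than in an individually randomized trial. Only ten units are randomized, and they come from three provinces where care use may differ. Cost is also part of the intended conclusion: the Abstract and the Discussion speak of an economic technology and a lower financial burden for patients. A chance difference between the arms in earlier care use would blur that conclusion, and the analyst could neither see it nor correct for it directly.

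**Working it through.** **1. Is there a pre-trial value anywhere?**
- Table 2, weeks −2 to −1: both rows empty.
- Table 3: later periods only.
- Economic evaluation: recording during the intervention.
- Table 1: earlier treatment and stroke history, but no falls, resource use or cost.

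So the document schedules none.

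**2. The plan's own figures.** The Sample size section gives 125 per group and 25 per CHC, and 125/25 = 5 CHCs per arm, as stated. The design effect is 1 + (25 − 1) × 0.05 = 2.2. The pooled SD is sqrt((2.8² + 3.33²)/2) = 3.076 and the difference is 8.5 − 6.5 = 2.0. The printed formula with two-sided 5% and 90% power then gives 49.7 × 2.2 = 109.4, so 110 per group; a two-sample t version gives 112 to 113. The plan states 114. Nothing below depends on this small gap, because the check uses the 125 as printed.

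**3. Chance difference between arms in an unrecorded baseline variable.** In SD units, SE = sqrt(2 × [1 + 24 × ICC]/125). The document gives 0.05 as the likely maximum ICC in the Berg scale calculation. Its use for costs or falls is an assumption, so a range is shown. The last column uses a normal approximation.

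| ICC (assumed) | SE of arm difference | Chance of a difference above 0.2 SD |
|---|---|---|
| 0.02 | sqrt(2 × 1.48/125) = 0.15 SD | 19% |
| 0.05 | sqrt(2 × 2.2/125) = 0.19 SD | 29% |
| 0.10 | sqrt(2 × 3.4/125) = 0.23 SD | 39% |

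Without clustering the SE would be sqrt(2/125) = 0.13 SD.

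**4. How much reaches the result.** A baseline difference d carries over as r × d, where r is the correlation between the pre-trial and later value. The document gives no r. For d = 0.2 SD and assumed r of 0.3, 0.5 and 0.7, the carry-over is 0.06, 0.10 and 0.14 SD.

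**5. What adjustment could regain.** At most it removes a share r² of the variance: 9%, 25% or 49% for the same three values. This is an upper range. It supposes that the covariate explains variation between CHCs as well as variation between patients, and it ignores what the recorded covariates already explain.

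**6. Why this should not be turned into extra patients.** At ICC 0.05 and 25 per CHC, the variance of a CHC mean is 0.05 + 0.95/25 = 0.088, of which 0.05/0.088 = 57% lies between CHCs. With the number of CHCs fixed at ten, more patients per CHC cannot reduce that part.

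**The case against.** The strongest reply is that nothing here is an error. Both rows stand in interval columns, like the adverse event row, because costs and falls accrue over time and have no value on a visit day. Only a recalled history could be taken at baseline. This stands, and the point is a design improvement, not a contradiction. A reader might set the sentence "All outcomes will be measured at baseline and 4-weeks, 8-weeks, 12-weeks, 6-week follow-up, and 12-week follow-up, respectively" against the empty cells. But that sentence belongs to the primary and secondary outcomes, and Table 2 lists costs and fall reports outside them.

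A reader might also infer that the arms' starting position cannot be adjusted for at all, or that a cost comparison would be biased. The document supports neither. Randomization keeps the comparison unbiased, and a standard error that respects clustering already contains the chance variation. Several related measures have a baseline mark: the Berg scale, Timed-Up-and-Go, Barthel Index, SF-36 and "Modified falls efficacy scale". The Background itself names balance problems as the strongest predictor of falling. These are proxies for function and confidence rather than for earlier spending or fall counts, so they narrow the gap without closing it.

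Nor does the missing-data plan fail. Its imputation uses baseline information in general and can run without earlier costs or falls, though with weaker predictors.

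Finally, self-reported falls are not a listed outcome, and the Statistical analysis section names no fall or cost model. The fall part is therefore conditional on falls being compared. The drug-use part is weaker still, because blood glucose and lipids have their own baseline and Table 1 records earlier treatment.

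**Conclusion.** The point holds in a limited form. As scheduled, a cost or fall comparison cannot be adjusted for its own pre-trial level. The consequence is some loss of precision, and of protection against chance imbalance, in the economic evaluation and in the descriptive fall data. The chance imbalance has an SE of about 0.19 SD at an assumed ICC of 0.05 (0.15 to 0.23 SD for 0.02 to 0.10), and only the fraction r of any imbalance reaches the result. Both the ICC for costs and falls and the value of r are assumptions, so the net loss cannot be stated as one number.

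The primary Berg scale analysis, the sample size and the validity of the randomized comparison are untouched. This is a cheap improvement of low priority.

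**What to change.** - In Table 2, add a mark at weeks −2 to −1 for both forms, with a fixed recall period (for example the previous 4 weeks, to match the first recording block). Apply it to patients not yet enrolled, before their first training session.
- Enter baseline resource use or cost as a covariate in the cost model, with the CHC random effect. Do the same with earlier falls if falls are compared.
- For patients already enrolled, treat the covariate as missing and do not collect it after exposure. The Trial status section says that recruitment has started, and the Blinding section says that participants cannot be blinded, so recall of earlier costs and falls could differ by arm.

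The cost is two existing forms completed once more at an existing visit: a few minutes of patient time, some recall error, and an incomplete covariate for the earliest patients. No other figure in the plan changes.

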**Table 3 Tab3:** **The second part of study flow**

**Items**		**Intervention period (weeks)**	**End of the exercise (weeks)**	**Follow-up (weeks)**	**Outcome assessment (weeks)**	**Follow-up (weeks)**	**End of the follow-up(weeks)**
		**9-12**	**12**	**13-18**	**18**	**19-24**	**24**
Recruitment							
Inclusion criteria							
Exclusion criteria							
Informed consent							
Basic characteristic variables							
Randomization and allocation concealment							
Primary outcomes	Berg balance scale		×		×		×
Secondary outcomes	Simplified Fugl - Meyer motor function assessment		×		×		×
	Modified barthel index		×		×		×
	The Medical outcomes study 36-Item Short-Form health survey		×		×		×
	Beck depression inventory		×		×		×
	Modified falls efficacy scale		×		×		×
	Single leg stance test		×		×		×
	Timed-Up-and-Go test		×		×		×
	Blood glucose and blood lipid		×				
	Proprioception function		×				
	Cardiopulmonary function		×				
	Gait analysis		×				
Adverse events recorded		×		×		×	
Medication and fall self-report		×		×		×	
Rehabilitation costs questionnaire		×		×		×	

### Primary outcome

Balance function will be assessed with BBS, which is identified as the most commonly used assessment tool across the continuum of stroke rehabilitation [31]. The Chinese version translated by Yan Tiebin and Jin Dongmei [32] will be used. The scale measures both static and dynamic aspects of balance though l4 items. Each item is scored from 0 to 4, with a score of 0 representing an inability to complete the task and a score of 4 representing independent item completion. A global score is calculated out of 56 possible points. A difference of 5.8 points on the BBS was required to conclude with 90% certainty that patients receiving stroke rehabilitation underwent a real change in balance [33].

### Secondary outcomes

Motor function will be measured by simplified Fugl-Meyer motor function assessment, which is reliable and valid, and often used in rehabilitation research studies [34-36]. The scale consists of 33 items that reflect upper-limb motor function and 17 items that reflect lower-limb motor function. Each item is scored on a 3-point rating scale and higher score indicate slighter motor impairment.Activities of daily living (ADL) will be assessed with the Modified Barthel Index (MBI). The Chinese version translated by Yan Tiebin, which is valid and reliable for use with older people post stroke [37] will be used. The scale includes 10 items, and evaluation results are on a 5-point ranging from 1 (completely dependent) to 5 (completely independent), with higher composite scores indicative of better ADL.The Medical Outcomes Study 36-Item Short-Form Health Survey (SF-36) will be administered to measure the physical and mental quality of life. The Chinese version of SF-36 translated by Zhejiang University will be used. The score range from 0 to 100, with higher scores indicating better health status [38].Depression will be measured by Beck Depression Inventory (BDI). Since depression is an abnormal state of the organism manifested by signs of symptoms such as low subjective mood, pessimistic and nihilistic attitudes, loss of spontaneity and specific vegetative signs, the scale is constructed to measure these components and to assess whether depression is to be the primary diagnosis [39]. BDI contains 21 groups of statements that describe mental conditions. Higher total scores stand for more severe depression.Fear of falling will be measured by the Modified Falls Efficacy Scale. The version translated by Hao Yanping and Liu Xueqin [40] will be used. The scale assesses the degree of perceived efficacy at avoiding falls during each of ten relatively nonhazardous activities of daily living. Lower scores indicate much more fear of falling.Single leg stance test will be served to measure static balance [41]. Individuals keep their eyes open, both hands on their hips, and their non-weight bearing limb in a slightly flexed position, as just not touching the floor. A stopwatch was used to record in seconds the duration of standing. Three test trials were conducted for each leg separately. The score of their best performance on each test was recorded. If a patient was not able to keep balance on one leg, the score was 0 sec.Timed-Up-and-Go Test will be administered to measure mobility function. This test has high sensitivity (87%) and specificity (87%) in screening seniors at risk of falls [42]. Subjects have to rise from sitting, walk 3 meters with assistive device or orthosis as needed, turn round, and return to the seat as fast as possible. A trained rater record the time for a participant to complete the task with a stopwatch.Blood glucose and blood lipid are high risk factors of stroke. The above two kinds of outcomes will be tested by therapist in Laboratories Center of The Rehabilitation Hospital Affiliated to FJTCM, The First Affiliated Hospital of Henan University of TCM , and The Second Affiliated Hospital of Shandong University of Traditional Chinese Medicine.Lumbar proprioception function and lower-limb proprioception function will be measured by the Prokin proprioception evaluation and training system (product type: PK254P) produced by Tecnobody .S.r.l, Italy.Cardiopulmonary function will be assessed by the step test, vital capacity, blood pressure, and heart rate. The assessments will be completed using step testers and vital capacity testers produced by Zhongtitongfang Co., Ltd., Beijing (product type: CSTF-FH-5000), electric sphygmomanometers produced by the Omron Corp, China (product type: HEM-746C).Three-dimensional gait analysis will be measured by the Gait Analysis Process ( OrthoTrak 6.6.1 and Foot 3D 1.0.) produced by Motion Analysis Corporation at [name] in USA.
